### 3.6. Statistial Analysis

Outcome data will be analyzed with the intention-to-treat approach. The distribution of outcome data will be assessed for normality using histograms. Paired and unpaired parametric continuous data will be analyzed with a two-way and one-way analysis of variance (ANOVA), respectively. Paired and unpaired non-parametric continuous outcome data will be analyzed with the Wilcoxon and Mann–Whitney U test, respectively.

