### 3.5. Outcomes

The primary outcomes are pain during movement, at night and at rest registered with VAS and global pain measured using the Knee injury and Osteoarthritis Outcome Score (KOOS) pain subscale. The secondary outcomes are KOOS disability and quality-of-life (QoL), analgesic usage, global health change, knee active range of motion (AROM), number of chair stands in 30 s, maximum pain-free isometric knee extension strength, joint line and tibia condyle pain pressure threshold (PPT) and real-time ultrasonography (RTU)-assessed suprapatellar effusion, meniscal neovascularization (Doppler) and femur cartilage thickness.

All the outcomes are assessed 0, 3, 8, 26 and 52 weeks after randomization, except for global health change, which is only evaluated at completed ST (week 8) (Table 1). The sequence of the assessment was typically as follows: Firstly, the participants filled out questionnaires, then ultrasonography was performed and lastly the physical examination was carried out.

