### 3.7. Sample Size

We expect a between-group difference in pain during movement of 20 mm VAS [12] and assume that the related standard deviations will be 14.85 mm in the intervention group and 13.93 mm in the control group at completed therapy [31,32,33]. We expect a between-group difference in pain at rest of 15 mm VAS [12] and assume that the related standard deviation will be 15.43 mm in the intervention group and 12.87 mm in the control group at completed therapy [31,32,33]. If correct, an 80% chance to detect a significant difference in pain during movement and pain at rest will require a total of 20 and 32 participants, respectively. A total of 50 subjects will be enrolled to increase the external validity and account for possible dropouts. No power calculation was made for pain at night and global pain (KOOS) as these have not been used as outcomes in a similar study.

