## 4. Discussion

This study will improve our understanding of what occurs with the local pathophysiology, tissue morphology and clinical status of persons with KOA up to a year after the initiation SET associated with LLLT.

Our study features a random and concealed group allocation, blinding of participants, assessors and therapists and intention-to-treat analysis, methods of high standard. Although previous studies of the current topic generally appear to have been conducted with low risk of bias, therapist blinding has often lacked [21,33,34,35,36,37]. Our study is not without limitations. Only one laser dose is tested out and other relevant inflammatory markers than meniscal neovascularisation (Doppler) and suprapatellar effusion are not evaluated, such as prostaglandin E2 and interleukin 1 and 6. Furthermore, the long-term results may be impacted by the use of contaminant interventions.

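### The named ANOVA and rank tests do not by themselves deliver the promised intention-to-treat analysis once visits are missed; one mixed model per continuous outcome would come closer

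*Protocol article*

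**What the plan says.** Section 3.6 opens with the population: "Outcome data will be analyzed with the intention-to-treat approach". It then fixes the tests. For data judged normal from histograms: "Paired and unpaired parametric continuous data will be analyzed with a two-way and one-way analysis of variance (ANOVA), respectively". Otherwise: "Paired and unpaired non-parametric continuous outcome data will be analyzed with the Wilcoxon and Mann–Whitney U test, respectively".

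Three other places bear on this:

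- Section 3.5 sets the schedule: "All the outcomes are assessed 0, 3, 8, 26 and 52 weeks after randomization". Global health change, at week 8 only, is the exception.
- Section 3.7 anticipates losses without giving a rate: "A total of 50 subjects will be enrolled to increase the external validity and account for possible dropouts".
- The Discussion counts the analysis population as a strength: "blinding of participants, assessors and therapists and intention-to-treat analysis, methods of high standard".

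The Introduction gives the lack of long-term assessment in earlier trials of this combination as the reason for the study. Section 2.1 says that follow-up is still running, and section 3.3 says that the treatment code is opened only after the analyses.

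**The concern.** An intention-to-treat claim covers everyone randomised, in the arm allocated. The four named tests handle a missing value in only two ways, both by leaving the person out:

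- A conventional repeated-measures ANOVA across visits removes a participant who misses any visit in the model.
- A one-way ANOVA or Mann–Whitney test at one visit removes those absent at that visit. It makes no use of baseline or earlier pain scores, although these are the data most likely to predict who left.

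The contrasts most exposed are weeks 26 and 52, which are what the trial sets out to add. If participants with more pain stop attending, and do so differently in the two arms, the arm difference among those who remain is biased. Even without bias, an unadjusted comparison at one visit gives up precision that the collected data could supply.

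**Working it through.** **1. The plan's own figures.** Section 3.7 assumes a 20 mm difference in movement pain, and that "standard deviations will be 14.85 mm in the intervention group and 13.93 mm in the control group at completed therapy". For rest pain it assumes 15 mm with SDs of 15.43 and 12.87 mm. Allocation is 1:1 (section 3.1). Alpha is not stated; I assume 0.05 two-sided.

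- Pooled SD, movement: √((14.85² + 13.93²)/2) = 14.40 mm.
- Pooled SD, rest: √((15.43² + 12.87²)/2) = 14.21 mm.
- Smallest totals with 80% power from the noncentral t distribution: 20 and 32. Both stated figures reproduce exactly.

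**2. Who stays in the analysis.** The article gives no dropout rate, so these are assumed ranges.

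Independent loss p at each of four follow-up visits, with complete cases = 50 × (1 − p)⁴:

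| p | Complete cases of 50 |
|---|---|
| 5% | 50 × 0.8145 = 40.7 |
| 10% | 50 × 0.6561 = 32.8 |
| 15% | 50 × 0.5220 = 26.1 |

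Monotone dropout of 4%, 8%, 14% and 20% by weeks 3, 8, 26 and 52:

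| Analysis | Participants used |
|---|---|
| Repeated-measures ANOVA across all visits | 40 at every visit |
| Separate test at each visit | 48, 46, 43, 40 |
| Mixed model, any follow-up value | 48 contribute |

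**3. Is power the problem?** Two-sided t-test power under the inputs of step 1:

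| Total N | Movement | Rest |
|---|---|---|
| 50 | 99.8% | 95.5% |
| 45 | 99.5% | 93.3% |
| 40 | 99.0% | 90.2% |
| 35 | 97.9% | 85.8% |
| 32 | 96.7% | 82.4% |

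Rest pain keeps 80% power down to 32 participants, a loss of 18/50 = 36%. Movement pain keeps it down to 20, a loss of 30/50 = 60%. Of the cases in step 2, only 15% independent loss per visit, analysed on complete cases, falls below 32. The planned power therefore largely survives.

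**4. How large could the bias be?** This is a deliberately severe illustration. Suppose the 20% with the highest week 8 pain in one arm leave and nobody leaves the other arm. With a normal distribution and SD 14.4 mm, the week 8 mean of those remaining falls by 14.4 × φ(0.8416)/0.80 = 14.4 × 0.280/0.80 = 5.0 mm. With the same SD assumed at week 52, the shift there is 5.0 × ρ, where ρ is the week 8 to week 52 correlation: 2.5 mm at ρ = 0.5 and 3.5 mm at ρ = 0.7 (assumed). A test at week 52 alone carries that shift. A correctly specified mixed model that includes week 8 removes it, because dropout here depends on an observed value.

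**5. Precision.** With 40 participants at week 52 (20 per arm) and SD 14.4 mm, the unadjusted standard error is 14.4 × √(2/20) = 4.55 mm. Adjusting for a baseline correlated r with the outcome multiplies it by about √(1 − r²): 4.34, 3.94 or 3.25 mm at assumed r = 0.3, 0.5 or 0.7. The entry requirement of at least 40 mm movement pain narrows the baseline range, so r for that outcome may be at the lower end.

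**The case against.** Much of the case on the other side stands.

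- **Section 3.6 does not say that one model spans five visits.** Its pairing of tests suggests that paired means change within a participant and unpaired means the comparison of arms. On that reading the week 52 contrast loses only those absent at week 52. A reader might infer that everyone with an incomplete record is discarded; the text does not support that.
- **Intention-to-treat in the sense of analysis by allocated arm is compatible with ANOVA**, and ANOVA after imputation could include all 50. A reader might infer that the promise and the methods exclude each other; they do not.
- **A reader might infer that the two-way ANOVA treats repeated values as independent and so inflates the type I error.** Section 3.6 assigns that test to paired data, which speaks against it.
- **A reader might infer that the participants enrolled beyond 32 are wasted.** Step 3 shows otherwise. The sample size was also calculated for completed therapy, not week 52.
- **A condensed article may leave missing-data handling to a fuller document.** Its absence alone is therefore no fault.
- **The 20% one-arm dropout is an extreme construction.** If departure depends on pain that was never recorded, a mixed model would not in general remove the bias either.

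What remains is a point about methods that are stated. The article names its tests, and none of them uses the baseline and earlier scores to protect the late contrasts. An analysis plan that follows the article would inherit that choice.

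**Conclusion.** The concern holds in a limited form. Without a further step, the named tests compare those observed, and the intention-to-treat label promises more than that once visits are missed. The consequence is possible bias and avoidable imprecision at weeks 26 and 52. Under the assumed patterns, between 26 and 41 of 50 would have complete data with 15% to 5% independent loss per visit, and 40 would be present at week 52 with 20% monotone dropout. The illustrative bias of 2.5 to 3.5 mm compares with a planned effect of 20 mm on movement pain. All of this rests on assumed dropout and correlations, and on carrying the completed-therapy SD to week 52. The change should be made, but the primary contrasts at completed therapy do not fail without it.

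**What to change.** For each continuous outcome, replace the two-way and one-way ANOVA with one mixed model for repeated measures:

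- Fixed effects: arm, visit, arm-by-visit, baseline and baseline-by-visit.
- Within-person covariance: unstructured, with heterogeneous compound symmetry as the named fallback if it does not converge.
- Population: by allocated arm, all randomised participants with any follow-up value.
- Estimates: the arm difference at weeks 3, 8, 26 and 52, read from this model.

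This set may still fall short of all 50. The plan should therefore say how participants with no follow-up value are accounted for: at least their number and reasons by arm, and their place in the sensitivity analysis. Add one sensitivity analysis in which those who leave do worse than the model predicts. If a rank test is kept for a skewed outcome, describe it as using only those observed at that visit.

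The cost is a wording change and a few hours of programming, with no new data. The downsides are a model slightly harder to explain than ANOVA and reliance on missing-at-random, which the sensitivity analysis probes. On the article's own account follow-up is ongoing and the code unbroken, so the change can be made without knowledge of the results.

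### A look at histograms decides whether each continuous outcome gets ANOVA or a rank test, so the primary method and effect measure are not fixed in advance

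*Protocol article*

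**What the plan says.** Section 3.6 sets the rule in three steps.

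- The look: "The distribution of outcome data will be assessed for normality using histograms".
- If the data are judged parametric: "Paired and unpaired parametric continuous data will be analyzed with a two-way and one-way analysis of variance (ANOVA), respectively".
- If not: "Paired and unpaired non-parametric continuous outcome data will be analyzed with the Wilcoxon and Mann–Whitney U test, respectively".

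The section names no effect measure for either branch and no baseline covariate. The rule covers continuous outcomes only. Analgesic use (section 3.5.4, dichotomous) and global health change (section 3.5.3, ordered categories) fall outside it.

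Section 3.7 sizes the trial on differences in means. For movement pain, "We expect a between-group difference in pain during movement of 20 mm VAS", with "standard deviations will be 14.85 mm in the intervention group and 13.93 mm in the control group at completed therapy". For rest pain, "We expect a between-group difference in pain at rest of 15 mm VAS", with "standard deviation will be 15.43 mm in the intervention group and 12.87 mm in the control group at completed therapy". These give totals of 20 and 32 for 80% power, and 50 are enrolled.

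There are four primary pain outcomes (section 3.5) and four post-baseline visits, at weeks 3, 8, 26 and 52 (Table 1). Section 3.3 keeps the real/placebo code concealed until the analyses are complete.

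**The concern.** The method for a primary outcome should be known before its data are seen. Here it follows from a visual judgement of the outcome data, and the two branches answer different questions. ANOVA compares means. Mann–Whitney compares the two distributions through the probability that a value from one group exceeds a value from the other.

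For paired data the gap is wider. A two-way ANOVA can hold group and time together. The paired Wilcoxon test is a one-sample test on within-person differences and has no group factor, so the longitudinal between-group comparison disappears and only separate Mann–Whitney tests remain.

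The trial sets out to describe short- and long-term effectiveness. If an outcome were analysed on means at one visit and on ranks at another, its course over the year could not be read on one scale. The mm difference that justified the sample size might not be reported where the rank branch is taken.

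**Working it through.** **1. What the trial was sized on.** The inputs are from section 3.7. Alpha and sidedness are not given; two-sided 0.05 is assumed.

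Pooled SD = √((s₁² + s₂²)/2):
- Movement: √((14.85² + 13.93²)/2) = √207.28 = 14.40 mm
- Rest: √((15.43² + 12.87²)/2) = √201.86 = 14.21 mm

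Normal approximation, n per arm = 2 × [SD × (1.960 + 0.842)/difference]²:
- Movement: 2 × 207.28 × 7.849/400 = 8.13, so 9 per arm, total 18
- Rest: 2 × 201.86 × 7.849/225 = 14.08, so 15 per arm, total 30

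The noncentral t distribution gives 10 and 16 per arm, totals **20 and 32** (power 83.6% and 82.4%), exactly as stated. One-sided testing (normal approximation) gives 14 and 24, which does not match. The design quantity is therefore a mean difference in mm, tested two-sided.

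**2. What the rank branch targets under the same assumptions.** P(superiority) = Φ(difference/√(s₁² + s₂²)):
- Movement: Φ(20/20.36) = 0.84
- Rest: Φ(15/20.09) = 0.77

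These are probabilities, not 20 mm and 15 mm.

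**3. Type I error at 25 per arm.** There were 20,000 simulated null trials per scenario, with a Shapiro–Wilk test in each arm standing in for the histogram. The VAS distributions are assumptions.

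| Null data | t-test | Mann–Whitney | Two-stage rule | Smaller p-value |
|---|---|---|---|---|
| Normal, mean 40, SD 14.2 | 5.1% | 4.9% | 5.2% | 6.0% |
| Normal, mean 12, SD 14.2, clipped at 0 | 5.0% | 4.8% | 4.9% | 6.0% |
| Gamma, mean 20, SD 14.2 | 4.9% | 4.6% | 5.1% | 6.2% |

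The t-test holds its level even with a floor at zero, so the switch buys no needed validity. The last column describes choosing by p-value, which section 3.6 does not propose.

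**4. How readily the method could switch.** If normality were judged separately for 4 outcomes × 4 visits = 16 looks, and the data were truly normal, a false call rate of 4.24% per look (simulated, n = 50) gives 1 − (1 − 0.0424)¹⁶ = 50% for at least one switch. This assumes independent looks and the Shapiro–Wilk stand-in.

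**5. Power and precision.** With 50 participants, t-test power is 99.8% (movement) and 95.5% (rest). The 95% CI half-width is 2.011 × SD × √(2/25), or 8.2 and 8.1 mm. Mann–Whitney would need totals of 22 and 34 (relative efficiency 0.955) or 24 and 38 (worst case 0.864), all below 50.

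**6. Where the branches part.** With assumed skewed data (gamma, SD 14.2, means 10 and 25), the mean difference is 15.0 mm, the median difference 17.9 mm and P(superiority) 0.84. Power is 92.8% for the t-test and 99.5% for Mann–Whitney, and the two disagree on significance in about 7% of trials.

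**The case against.** Much can be said for the plan, and most of it stands.

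- **Error rate.** A reader might infer that choosing the test from the data inflates false positives. A distribution-driven rule stays near 5%. About 6% arises only if the better p-value is taken.
- **No mm estimate possible.** A reader might infer that the rank branch cannot give one. It can: the Hodges–Lehmann shift is in mm and in the skewed example is about 15.2 mm against a mean difference of 15.0 mm. Means can also be reported beside a rank test. What stands is that the article commits to neither.
- **Lost baseline adjustment.** The histogram rule does not cause this, because the ANOVA branch names no baseline covariate either.
- **Steering.** With the code concealed, the analyst cannot choose a test to favour active laser. The coded groups can still be compared, so this limits the concern without removing it.
- **Switching by visit.** The text permits it but does not state it. Nor does it say whether raw values, changes or residuals are inspected. A pile-up of rest or night pain near zero is plausible, since the 40 mm entry minimum covers movement pain only, but the documents do not show it.
- **Detail left elsewhere.** A numerical criterion and the unit of inspection may be in a fuller document, and their absence is not the point. The point is the rule that section 3.6 does state.

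**Conclusion.** The concern holds in limited form and should be acted on. Section 3.6 makes the primary method, and with it the effect measure, depend on the observed data, while section 3.7 sized the trial on a mean difference. The exact match to 20 and 32 rests on an assumed two-sided alpha of 0.05.

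The harm is to pre-specification, comparability across visits and the estimand. The documents do not support a claim of material type I inflation, inadequate power or an intention to switch methods between visits. The error-rate result rests on the assumed distributions and on Shapiro–Wilk in place of a visual judgement. The 50% switching figure is illustrative and assumes 16 separate, independent looks.

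**What to change.** Before the code is broken, and as a dated change to section 3.6:

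1. Drop the histogram rule for the VAS and KOOS pain outcomes.
2. State one baseline-adjusted linear or mixed model for all of them, reporting the between-group mean difference with 95% CI at each visit.
3. Check residuals, and use a rank test or bootstrap CI as sensitivity analysis only.
4. Name in advance any outcome expected to be mostly zeros, for example Doppler pixel area, for a rank-based test.

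Baseline adjustment is a separate gain, since neither current branch includes it. The variance removed is r²: 0.3² = 9% to 0.7² = 49% if the baseline correlation is 0.3 to 0.7 (assumed; the article gives none).

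**Cost.** The text is short and needs no new data or participants, because baseline values are already collected. Section 2.1 reports the intervention complete and follow-up ongoing, so the change must be documented as made before unblinding. The statistical downside is some power lost against a rank test if residuals are heavily skewed: 92.8% against 99.5% in the skewed example above, before any gain from baseline adjustment.

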## 3. Procedure

### 3.1. Randomization

Eligible subjects willing to participate in the trial were randomly divided in two parallel groups, one group with ST and LLLT and one group with ST and placebo LLLT. This was carried out after the baseline assessment by drawing of concealed opaque envelopes, each containing a red or green label (group code). The envelopes were prepared by an assistant who will not otherwise be involved in the study. The allocation ratio was 1:1.

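### The between-arm test named for continuous outcomes has no place for the baseline value; ANCOVA on the week-0 score would gain precision at almost no cost

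*Protocol article*

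**What the plan says.** On the analysis of continuous outcomes, section 3.6 says: "Paired and unpaired parametric continuous data will be analyzed with a two-way and one-way analysis of variance (ANOVA), respectively". For data judged non-normal it says: "Paired and unpaired non-parametric continuous outcome data will be analyzed with the Wilcoxon and Mann–Whitney U test, respectively". The comparison of the two arms is the unpaired case, so it falls to one-way ANOVA or Mann–Whitney U. The section mentions no covariate, ANCOVA, change score or group-by-visit interaction.

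On the data available, section 3.5 says: "All the outcomes are assessed 0, 3, 8, 26 and 52 weeks after randomization, except for global health change". Table 1 ticks week 0 in 15 of its 16 rows. Section 3.1 says of the allocation: "This was carried out after the baseline assessment by drawing of concealed opaque envelopes". Baseline is therefore measured before allocation, and no stratification on pain is described.

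On the planned contrast, section 3.7 states "We expect a between-group difference in pain during movement of 20 mm VAS", with "standard deviations will be 14.85 mm in the intervention group and 13.93 mm in the control group at completed therapy", and "We expect a between-group difference in pain at rest of 15 mm VAS". The SDs refer to the end of therapy, and no baseline SD or baseline-to-follow-up correlation is given.

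**The concern.** A one-way ANOVA has a single factor. With two arms it is the two-sample t-test and cannot take a covariate; Mann–Whitney U is unadjusted in the same way. A pre-randomization measurement of the same outcome is usually among the best predictors of the follow-up value, and here it is already in hand.

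Two things are at stake. The first is precision: variation between participants that baseline would explain stays in the error term, so the confidence interval is wider than the data require. The second is conditional accuracy: if the arms happen to differ at week 0, part of that difference carries into the follow-up comparison.

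Both matter most where the margin is thinnest. The expected effects in section 3.7 apply at completed therapy. No effect size is given for weeks 26 and 52, and no power calculation was made for night pain or KOOS pain, which are also primary.

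**Working it through.** **Inputs from section 3.7 and section 3.1.** Movement pain: difference 20 mm, SDs 14.85 and 13.93 mm. Rest pain: difference 15 mm, SDs 15.43 and 12.87 mm. Power 80%, allocation 1:1, 50 enrolled (25 per arm, before dropout).

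**Assumptions.** Two-sided alpha of 0.05 (not stated). Correlation r between baseline and follow-up of 0.3 to 0.7 (not stated). For the imbalance figures, a baseline SD equal to the end-of-therapy SD.

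**1. Reproduce the stated sample size.**
- Pooled SD, movement: √[(14.85² + 13.93²)/2] = 14.40 mm.
- Pooled SD, rest: √[(15.43² + 12.87²)/2] = 14.21 mm.
- An unadjusted two-sample t-test needs 9.20 and 15.11 per arm. Rounded up, the totals are 20 and 32, exactly as stated.

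The sample size therefore rests on an unadjusted comparison of follow-up scores. That supports reading the one-way ANOVA in the same way.

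**2. Power of the planned test with 50 participants.** 99.8% for 20 mm in movement pain and 95.5% for 15 mm in rest pain.

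**3. Gain from ANCOVA.** The residual variance is (1 − r²) times the unadjusted variance, so the cut is r². The unadjusted SE for movement pain is 14.40 × √(2/25) = 4.07 mm. The effective N is 50/(1 − r²).

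| r | Variance cut | SE, movement (mm) | 95% CI half-width (mm) | Effective N |
|---|---|---|---|---|
| unadjusted | – | 4.07 | 8.2 | 50 |
| 0.3 | 9% | 3.88 | 7.8 | 55 |
| 0.5 | 25% | 3.53 | 7.1 | 67 |
| 0.7 | 49% | 2.91 | 5.9 | 98 |

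For rest pain the SE falls from 4.02 mm to 3.83, 3.48 and 2.87 mm.

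For a smaller true effect of 10 mm (illustrative only), power for movement pain rises from 67% to 71%, 79% and 92% at r = 0.3, 0.5 and 0.7.

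**4. Effect of a chance imbalance.** With equal SDs, the SE of the baseline difference is also 4.07 mm. An imbalance of k SEs shifts the unadjusted estimate by r × k × 4.07 mm. The conditional type I error is P(|N(rk, 1 − r²)| > 1.96).

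- k = 1, r = 0.5: shift 0.5 × 4.07 = 2.0 mm. Conditional type I error is 5.0%, 4.8% and 3.9% at r = 0.3, 0.5 and 0.7, so there is no inflation.
- k = 2, r = 0.5: shift 0.5 × 2 × 4.07 = 4.1 mm. Conditional type I error is about 8%, 13% and 22% at r = 0.3, 0.5 and 0.7. An imbalance this large or larger occurs in about 5% of randomizations.
- k = 0, r = 0.5: about 2.4%, below nominal. Averaged over all randomizations the error is 5%.

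**5. Would a change score do instead?** Its variance relative to the follow-up score is 2(1 − r), which is 1.4, 1.0 and 0.6 at r = 0.3, 0.5 and 0.7. The ANCOVA factors are 0.91, 0.75 and 0.51. A change score is worse than ignoring baseline when r < 0.5. Since 2(1 − r)/(1 − r²) = 2/(1 + r) is at least 1, it is never better than ANCOVA.

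**The case against.** The strongest reply is that section 3.6 does not say which values enter the one-way ANOVA. Change scores would use baseline. So would the group-by-visit interaction of the two-way ANOVA, since group and visit are the natural two factors for paired data in this design. It would be wrong to dismiss the two-way ANOVA because including week 0 dilutes the group effect: that holds for the group main effect, not for the interaction. This part of the reply stands. However, neither reading is stated, the two-way ANOVA is assigned to paired data, and the sample size matches an unadjusted comparison of follow-up scores. For one follow-up visit, the interaction with week 0 is the difference in mean change, so step 5 of the working applies to it too.

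A second reply is that a short article may leave covariates to a fuller plan. That would answer a complaint about silence. Here the article names a method, and that method excludes a covariate.

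A reader might go further and infer that the planned analysis is biased, that its type I error is inflated, that imbalance is likely, or that the trial is underpowered. The documents support none of these. Randomization keeps the unadjusted estimate unbiased on average with nominal error, the 13% figure needs an uncommon imbalance, and power for the planned effects is high.

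The size of the gain is also uncertain. The 14.4 mm SD is an end-of-therapy figure, and the entry criterion of at least 40 mm movement pain (section 2.2) may lower both the baseline SD and r for that outcome. At r = 0.3 the gain is only 9%.

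**Conclusion.** The point holds as a free improvement, not as the correction of an invalid analysis. The between-arm tests named in section 3.6 cannot adjust for a baseline value that is collected before randomization. The price is a variance that is larger than necessary: ANCOVA would remove about 9% to 49% of it for r between 0.3 and 0.7, making 50 participants work like about 55 to 98. A typical 1-SE imbalance would leave about 2 mm in the unadjusted movement-pain estimate at r = 0.5, and an uncommon 2-SE imbalance about 4 mm.

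These figures rest on an assumed r, 25 analysed per arm and, for the imbalance, a baseline SD equal to the end-of-therapy SD. That ANCOVA is at least as efficient as either the follow-up score or the change score does not depend on the value of r, apart from the single degree of freedom. The point does not apply to global health change, which has no baseline, or to analgesic use, which is dichotomous.

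**What to change.** In section 3.6, for every continuous outcome with a week-0 value, replace the one-way ANOVA by an ANCOVA of the follow-up value on arm and that outcome's own week-0 value. A mixed model over the post-baseline visits with baseline as a covariate would serve equally well. Report the adjusted between-arm difference with its 95% CI. If Mann–Whitney U stays as the fallback, say that it is unadjusted.

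The cost is one sentence and one degree of freedom, with no new data. According to the article, follow-up was still ongoing (section 2.1) and the treatment code stays concealed until the analyses are complete (section 3.3), so the change could be fixed and dated while blinded.
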